# The efficacy of polyglycolic acid felt reinforcement in preventing postoperative pancreatic fistula after pancreaticojejunostomy in patients with main pancreatic duct less than 3 mm in diameter and soft pancreas undergoing pancreatoduodenectomy (PLANET-PJ trial): study protocol for a multicentre randomized phase III trial in Japan and Korea

**DOI:** 10.1186/s13063-019-3595-x

**Published:** 2019-08-09

**Keywords:** Pancreatoduodenectomy, Pancreaticojejunostomy, Postoperative pancreatic fistula, Polyglycolic acid felt, International multicentre study

## Abstract

**Background:**

Partial pancreatoduodenectomy is performed for malignant and benign diseases of the pancreatic head region. The procedure is considered highly difficult and highly invasive. Postoperative pancreatic fistula (POPF) is an important complication because of several consequent complications, including intraabdominal haemorrhage, often increasing hospital stays and surgical mortality. Although many kinds of pancreaticojejunostomy aimed at reducing POPF have been examined to date, the technique has not yet been standardized. We devised a new method using double-coated polyglycolic acid felt after pancreaticojejunostomy. The aim of the PLANET-PJ trial is to evaluate the superiority of polyglycolic acid felt reinforcement in preventing POPF after pancreaticojejunostomy in patients undergoing partial pancreatoduodenectomy to previous anastomosis methods.

**Methods:**

Patients diagnosed with pancreatic or periampullary lesions in whom it is judged that the main pancreatic duct diameter was 3 mm or less on the left side of the portal vein without pancreatic parenchymal atrophy due to obstructive pancreatitis are considered eligible for inclusion. This study is designed as a multicentre randomized phase III trial in Japan and the Republic of Korea. Eligible patients will be centrally randomized to either group A (polyglycolic acid felt reinforcement) or group B (control). In total, 514 patients will be randomized in 31 high-volume centres in Japan and Republic of Korea. The primary endpoint is the incidence of POPF (International Study Group of Pancreatic Surgery grade B/C).

**Discussion:**

The PLANET-PJ trial evaluates the efficacy of a new method using double-coated polyglycolic acid felt reinforcement for preventing POPF after pancreaticojejunostomy. This new method may reduce POPF.

**Trial registration:**

ClinicalTrials.gov, NCT03331718. University Hospital Medical Information Network Clinical Trials Registry, UMIN000029647. Registered on 30 November 2017. https://upload.umin.ac.jp/cgi-open-bin/ctr/ctr_view.cgi?recptno=R000033874

**Electronic supplementary material:**

The online version of this article (10.1186/s13063-019-3595-x) contains supplementary material, which is available to authorized users.

## Background

Partial pancreatoduodenectomy is performed on malignant and benign diseases of the pancreatic head region. The procedure is considered highly difficult and highly invasive. Pancreaticojejunostomy requires a high level of surgical technique for anastomosing the residual pancreas and jejunum. When implementing partial pancreatoduodenectomy, a high-volume centre with highly skilled surgeons is recommended. The incidence of complications after partial pancreatoduodenectomy is reported to be 30–65%, higher than those of other digestive tract surgeries [1–10]. Among these complications, postoperative pancreatic fistula (POPF) is generally recognized as an important complication, because intraabdominal haemorrhage can be fatal. Increases in postoperative hospital stay and surgical mortality rates are also problems.

POPF was first standardized and reported in 2005 [11]. According to the latest International Study Group of Pancreatic Surgery (ISGPS) criteria reported in 2016 [12], the former “grade A POPF” is now redefined and called a “biochemical leak” because it has no clinical importance and is no longer referred to a true pancreatic fistula. Therefore, POPF has only grade B and grade C. Grade B requires a change in the postoperative management; drains are either left in place for > 3 weeks or repositioned through endoscopic or percutaneous procedures. Grade C refers to those POPFs that require reoperation or lead to single or multiple organ failure and/or mortality attributable to the pancreatic fistula.

Pancreaticojejunostomy generally involves a combination of suture between the pancreatic parenchyma and the seromuscular layer of the jejunum, and duct-to-mucosa suture. A clinical study regarding the various kinds of pancreaticojejunostomy was reported for the purpose of lowering the frequency of POPF; nevertheless, the frequency of more than grade B POPF remains approximately 10–20% [13–15]. In soft pancreas patients with unexpanded pancreatic ducts, the risk is further elevated to over 30% [16].

Polyglycolic acid (PGA) felt is a felt-like absorbable suture-reinforcing material. It is generally used to reinforce sutures of fragile tissues such as the lung, bronchi, liver and gastrointestinal tract and to reinforce a wide range of tissue defects. Regarding pancreaticojejunostomy using a PGA felt, the incidence of POPF formation was lower in some retrospective studies [17, 18]; on the other hand, no significant difference was found other studies [19, 20]. As already described, pancreaticojejunostomy with reinforcement of a PGA felt aimed at reducing POPF has yet to be fully examined.

We reported significant decreases of POPF thanks to the ingenuity of pancreaticojejunostomy in a single-institution matched historical-control study [21]. In distal pancreatectomy, we have verified the effect of oral food intake on POPF [22], and are participating in a multicentre prospective randomized trial associated with POPF [23].

Here, we have devised a new method using double-coated PGA felt for pancreaticojejunostomy in patients with a small diameter of the main pancreatic duct. This study is a multicentre randomized phase III trial in Japan and Republic of Korea to verify the usefulness of this double coating of PGA felt preventing POPF.

## Methods/design

### Aim

The aim of the PLANET-PJ trial is to evaluate the efficacy of PGA felt reinforcement in preventing POPF after pancreaticojejunostomy in patients with a main pancreatic duct less than 3 mm in diameter and a soft pancreas undergoing partial pancreatoduodenectomy.

### Study population

Patients undergoing pancreaticojejunostomy without a dilated main pancreatic duct (MPD) (so-called soft pancreas) and parenchymal atrophy or pancreatitis are eligible. There are no restrictions to the type of disease. Detailed eligibility criteria are presented in Table 1.

**Table 1 Tab1:** Eligibility criteria

Inclusion criteria	
(1) Pancreatic or periampullary lesions requiring pancreatoduodenectomy	
(2) Planned pancreaticojejunostomy including duct-to-mucosa anastomosis	
(3) Main pancreatic duct diameter ≤ 3 mm on the left side of the portal vein on preoperative imaging (computed tomography or magnetic resonance imaging)	
(4) Performance status (Eastern Cooperative Oncology Group scale): 0–1 at the time of enrolment	
(5) Age 20 years or older	
(6) Adequate organ function	
(a) Leukocyte count ≥ 2500 mm^3^, ≤ 14000 mm^3^	
(b) Haemoglobin ≥ 9.0 g/dl	
(c) Platelet count ≥ 100,000 mm^3^	
(d) Total bilirubin ≤ 2.0 mg/dl (does not apply to patients with obstructive jaundice)	
(e) Creatinine ≤ 2.0 mg/dl	
(7) Ability to understand and willingness to sign written informed consent document	
Exclusion criteria	
(1) Planned pancreatogastrostomy	
(2) Laparoscopic or laparoscope-assisted pancreatoduodenectomy	
(3) Pancreatic parenchymal atrophy or calcification due to chronic pancreatitis	
(4) Neoadjuvant treatment including chemotherapy or radiotherapy	
(5) History of upper abdominal surgery (both of open and laparoscopic) except cholecystectomy	
(6) Emergency surgery	
(7) Arterial reconstruction such as superior mesenteric artery, common hepatic artery or celiac artery	
(8) Severe ischaemic heart disease	
(9) Severe liver dysfunction due to liver cirrhosis or active hepatitis	
(10) Severe respiratory disorder requiring oxygen	
(11) Chronic renal failure with dialysis	
(12) Requiring resection of other organs (liver or colon) during pancreatoduodenectomy	
(13) Immunosuppressive treatment	
(14) History of severe hypersensitivity to polyglycolic acid felt or fibrin glue	
(15) Other severe drug allergies	
(16) Contrast media allergy for both iodine and gadolinium	
(17) Active duplicate cancer thought to affect adverse events	
(18) Severe psychological or neurological disease	
(19) Drug or alcohol abuse	
(20) Planned use of octreotide	

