### Randomization

After confirmation of eligibility, including written informed consent, patients are randomized in a 1:1 allocation ratio to either group A (polyglycolic acid felt reinforcement) or group B (control), preoperatively. Central randomization and registration will be applied, using the Electronic Data Capture (EDC) system (Seoul National University, Medical Research Collaborating Center). After being assessed for eligibility at registration, patients will be centrally randomized to either group A or group B. To minimize background bias between the two groups, this study is stratified for institution and suturing method to approximate the pancreas and the jejunum (mattress or non-mattress). We use Pocock and Simon’s minimization method for random assignment and the Mersenne Twister for random number generation. See Fig. 1 for a flow diagram of the PLANET-PJ trial.

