### Statistical analysis plan

All statistical analyses will be performed using the full analysis set (FAS) under the intention-to-treat principle. The significance level of this test is 5% (two-sided) and the confidence coefficient is 0.95. The Wilcoxon rank-sum test will be used for comparison of continuous variables. The Fisher’s exact test will be used for comparison of categorical variables. Kaplan–Meier curves will be used to represent time-to-event variables, and hazard ratios and 95% confidence intervals will be estimated by the Cox proportional hazard model. *P* < 0.05 will be considered significant.

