## Discussion

Partial pancreatoduodenectomy is an advanced procedure requiring a high level of surgical technique. With the development of surgical techniques and perioperative management in recent years, surgical-related mortality rates have become less than 5%. Nevertheless, the incidence of complications remains high at 30–65% [1–10]. In particular, the high frequency of POPF is problematic, because the various complications according to POPF, including intraabdominal haemorrhage or intraabdominal abscess, can be fatal.

There is no evidence to prove a safe and reliable procedure of pancreaticojejunostomy. We planned this study to evaluate the efficacy of a new method using double-coated PGA reinforcement to prevent POPF after pancreaticojejunostomy. This trial is a multicentre randomized phase III trial in Japan and Republic of Korea that is the first international study in pancreatic surgery. This study is designed to evaluate the usefulness of group A (double coating of PGA felt) compared with group B (without PGA felt) in terms of the frequency of POPF as the primary endpoint. Upon randomization, the eligible subjects will be stratified by the institution and suturing method to approximate the pancreas and the jejunum (mattress or non-mattress). The reason is that these factors may affect the incidence of POPF. Therefore, we will set these two factors for allocation in this study for appropriate analysis and evaluation. Moreover, we randomize the patients preoperatively after evaluating appropriateness in the CT image just before surgery. It would be ideal to randomize during surgery after the measurement of the diameter of the main pancreatic duct, but this is very difficult because of the situation of the participating facilities in this study.

All patients are blinded to the surgical approach that they will be receiving, and they are required to sign an informed consent before enrolling in this study [24]. However, blinding of the surgeons is not possible, owing to the different techniques used during the operation. This can be a potential source of inevitable bias. The anastomotic drains will be placed in all enrolled patients because measurement of the amylase level in the anastomotic drains is required for assessment of POPF, although recent meta-analysis revealed that pancreatic resection with or without abdominal drainage results in similar rates of mortality, morbidity and reintervention [30].

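### The stated comparison of POPF uses no covariates, although preoperative duct diameter is known for every patient before allocation; adjusting for it may gain a little precision at almost no cost

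*Protocol article*

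**What the plan says.** All places are in the protocol article.

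- **Study population, Table 1, inclusion criterion 3:** "Main pancreatic duct diameter ≤ 3 mm on the left side of the portal vein on preoperative imaging", by CT or MRI.
- **Discussion, timing of allocation:** "we randomize the patients preoperatively after evaluating appropriateness in the CT image just before surgery". The imaging diameter is therefore a true baseline value.
- **Randomization:** "this study is stratified for institution and suturing method to approximate the pancreas and the jejunum (mattress or non-mattress"), and "We use Pocock and Simon’s minimization method for random assignment". Diameter is not a factor. The Discussion gives the reason for the two chosen factors: each may influence how often POPF occurs.
- **Background:** POPF of grade B or worse is put at about 10–20% in general, and then "In soft pancreas patients with unexpanded pancreatic ducts, the risk is further elevated to over 30" per cent.
- **Statistical analysis plan:** all analyses are on the full analysis set by intention to treat, and Fisher's "exact test will be used for comparison of categorical variables". The only regression model named is Cox, for time-to-event variables.
- **Endpoints:** subgroup analyses are planned by anastomosis or pancreatic stent, not by diameter.
- **Interventions, Surgical procedure:** the duct is measured again in theatre, after allocation.

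**The concern.** POPF is binary, so the one comparison that the article states for it is unadjusted. That is a stated method, not a silence left to a later document. The article restricts entry on diameter, conditions both planning rates on it, rechecks it in theatre and measures it again at 3 months. It also reasons that factors which may affect POPF deserve attention in the design. A baseline value of that standing, already available at no cost, is not used in the stated analysis.

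Two things are at stake, both modest. If diameter still predicts POPF within the range up to 3 mm, the treatment effect is estimated a little less precisely than it could be. And if the arms differ by chance on diameter, the stated analysis has no means of allowing for it; an adjustment added after unblinding would carry less weight than one fixed beforehand. Analysing by the two minimisation factors would not cover this, because diameter is not one of them.

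**Working it through.** **1. Reproduce the plan's sample size.** Inputs from Sample size estimation: 26% v 15.5%, two-sided alpha 0.05, power 80%, 1:1. Normal formula with unpooled variance:

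n = (1.960 + 0.842)² × (0.26 × 0.74 + 0.155 × 0.845) / (0.105)² = 7.849 × 0.3234 / 0.011025 = 230.2, so 231 per arm.

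Inflation: 231 / 0.9 = 256.7, so 257 per arm and 514 in total. Both stated figures reproduce.

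**2. Power of the stated test.** Exact calculation for Fisher's test gives 76.8% at 231 per arm and 81.2% at 257 per arm, with an actual size of about 3.9%. This is context only: the gap to 80% at 231 per arm comes from Fisher's conservatism, not from leaving diameter out.

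**3. Gain from adjusting for diameter.** The article gives neither the distribution of diameter within 3 mm nor a risk gradient across it. Both are therefore assumed here: an odds ratio (OR) for POPF per mm wider duct of 0.7, 0.5 or 0.4, and either a uniform distribution on 1–3 mm or whole-mm readings of 1/2/3 mm in 25/40/35% of patients. Setup: 231 per arm, marginal rates held at 26% and 15.5%, 20,000 simulated trials per scenario, likelihood-ratio tests from a logistic model with and without diameter.

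| Diameter | OR per mm | Unadjusted | Adjusted | Gain (points) |
|---|---|---|---|---|
| Uniform | 0.7 | 80.0% | 80.0% | 0.0 |
| Uniform | 0.5 | 79.8% | 80.7% | 0.9 |
| Uniform | 0.4 | 79.7% | 81.4% | 1.7 |
| 1/2/3 mm | 0.7 | 80.7% | 80.9% | 0.2 |
| 1/2/3 mm | 0.5 | 80.4% | 82.0% | 1.6 |
| 1/2/3 mm | 0.4 | 80.4% | 83.3% | 2.9 |

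A repeat with 8,000 trials per scenario gave gains of 0.2, 0.7 and 1.4 points (uniform) and 0.3, 1.3 and 2.8 points (1/2/3 mm).

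A separate simulation (5,000 trials, uniform diameter) widened the gradient and compared an unadjusted z test with the adjusted model. At odds ratios of 1, 1.5, 2, 3 and 5 per mm *narrower* duct, power was 79.4 v 79.1%, 80.0 v 80.1%, 79.6 v 80.1%, 79.9 v 82.4% and 79.7 v 84.7%. The variance ratio for the risk difference (unadjusted over adjusted) was 1.00, 1.00, 1.02, 1.06 and 1.13. Type I error was about 5% with and without adjustment.

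**4. Size of a chance imbalance at 257 per arm.** The 95% limit for the difference in mean diameter is 1.96 × SD × √(2/257), with √(2/257) = 0.0882.

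- Uniform: SD = 2/√12 = 0.58 mm, limit 0.10 mm.
- 1/2/3 mm: mean 2.10, variance 5.00 − 4.41 = 0.59, SD 0.77 mm, limit 0.13 mm.

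The approximate shift in the POPF difference is limit × |ln OR| × 0.26 × 0.74:

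- smallest: 0.0998 × 0.357 × 0.1924 = 0.7 points;
- largest: 0.1328 × 0.916 × 0.1924 = 2.3 points.

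The planned difference is 26 − 15.5 = 10.5 points. These are 95% limits, not expected shifts.

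**The case against.** The case on the other side is strong in several respects.

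- **The premise within 3 mm is not documented.** The Background contrast is drawn across all patients and combines soft texture with an undilated duct. The entry criteria already remove most of that contrast. A reader might infer that diameter is the main driver of POPF among these patients and that precision is certainly lost; the article supports neither. This stands, and it is why the gain is given as a range that starts at nil.
- **Chance imbalance is not bias.** Randomisation keeps the unadjusted test valid, and its error rate and confidence interval already allow for such imbalance. This stands. What remains is that the stated analysis cannot correct an imbalance once it is seen.
- **Minimisation.** A short factor list that already includes institution is defensible. A reader might take the omission of diameter as a design error; it is not. The Discussion's remark that intraoperative randomisation would be preferable, read with the theatre recheck, concerns confirming the 3 mm limit. It does not present diameter within that limit as a covariate.
- **Measurement error.** Readings come from CT or MRI across 31 centres, and the protocol itself rechecks them in theatre. Error in the readings would flatten the gradient and shrink the gain. This stands.
- **The SAP is not shown.** It may contain an adjusted analysis. The article does, however, name the test for categorical endpoints, so the comment applies to a stated choice. If the SAP already adjusts for diameter, only the wording needs reconciling.
- **A model with diameter alone would ignore the design factors.** Correct; suturing method and institution belong in it.

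**Conclusion.** The point holds as a low-severity improvement. A baseline value that the trial already obtains in every patient is unused in the stated POPF comparison. Using it would add about 0 to 3 points of power over an unadjusted logistic model at assumed odds ratios of 0.7 to 0.4 per mm, and nothing if risk is flat within 3 mm. A chance imbalance at its 95% limit would move the difference by about 0.7 to 2.3 points against a planned 10.5, under the same assumptions.

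One comparison could mislead. Adjusted power of 80–83% against 76.8% for Fisher's test at 231 per arm should not be read as the benefit of adjusting for diameter, because most of that gap comes from leaving Fisher's test. Nothing here makes the planned test invalid or calls for a larger sample.

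**What to change.** Before any unblinding, including that for the interim analysis, prespecify the primary POPF comparison as a logistic regression on arm with these terms:

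- preoperative imaging duct diameter, continuous, in mm;
- suturing method (mattress or non-mattress), as declared at allocation;
- institution, handled in a way that tolerates small centres, for example as a random effect or pooled.

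Report the standardised risk difference with its 95% CI, so that the result stays on the scale of the planned 10.5 points. Keep the unadjusted comparison as supportive. Do not use the intraoperative diameter as a covariate: it is measured after allocation, and the surgeon is not blinded.

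Cost: a short text change in the analysis section or SAP, slightly more analysis work, and one numeric field in the EDC system if it records only that the criterion is met. No added patients, visits or procedures, and no change to the sample size or the minimisation.

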### Study design

This study is designed as a multicentre randomized phase III trial in Japan and Republic of Korea. A total of 514 patients will be included, and 31 leading institutions and hospitals in Japan and Republic of Korea will participate in the PLANET-PJ trial (Additional file 1). The registration period is scheduled for 3 years, and the follow-up period will be 3 months.

### Randomization

After confirmation of eligibility, including written informed consent, patients are randomized in a 1:1 allocation ratio to either group A (polyglycolic acid felt reinforcement) or group B (control), preoperatively. Central randomization and registration will be applied, using the Electronic Data Capture (EDC) system (Seoul National University, Medical Research Collaborating Center). After being assessed for eligibility at registration, patients will be centrally randomized to either group A or group B. To minimize background bias between the two groups, this study is stratified for institution and suturing method to approximate the pancreas and the jejunum (mattress or non-mattress). We use Pocock and Simon’s minimization method for random assignment and the Mersenne Twister for random number generation. See Fig. 1 for a flow diagram of the PLANET-PJ trial.

### Endpoints

This clinical trial will primarily evaluate the incidence of POPF. The secondary endpoints will be the length of drain placement after surgery, length of the hospital stay after surgery, incidence of overall biochemical leak and POPF, incidence of POPF by each suturing method to approximate the pancreas and the jejunum, incidence of delayed gastric emptying (DGE), incidence of intraabdominal abscess, incidence of post-pancreatectomy haemorrhage (PPH), incidence of interventional drainage, incidence of overall postoperative complications, incidence of POPF-related complications (POPF + DGE + abscess + PPH), incidence of 3-month mortality and incidence of reoperation.

Biochemical leak, POPF [12], DGE [25] and PPH [26] are defined and graded according to the International Study Group of Pancreatic Surgery (ISGPS) criteria and Clavien–Dindo classification [27]. Postoperative complications other than POPF, DGE and PPH are graded according to Clavien–Dindo classification [27]. Then, the comprehensive complication index was evaluated as a secondary outcome [28].

Subgroup analyses will be planned per anastomosis or pancreatic stent. These secondary outcomes will be exploratory.

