### Sample size estimation

This trial was designed to evaluate the efficacy of group A compared with group B in terms of the incidence of POPF. In cases using PGA felt at the pancreaticojejunostomy in partial pancreatoduodenectomy with an MPD diameter of 3 mm or less, the incidence of POPF was 15.5% [18, 19]. The incidence of POPF was 26% in a previous report without PGA felt at the pancreaticojejunostomy in partial pancreatoduodenectomy with an MPD diameter of 3 mm or less [29]. When statistical analysis is performed for a significance level of α = 0.05 (two-sided) in a superiority design, 231 patients are calculated to be required per arm, with a power 100(1 – β) of more than 80%, under the assumption that a small number of patients may be deemed ineligible and may thus be excluded from the analysis. Furthermore, as approximately 10% of the patients are expected to be ineligible for surgery, the sample size was eventually increased to 514 patients (257 patients per arm). This sample size was calculated using software PASS 15.0.6.

In the evaluation of the secondary endpoints, a hypothesis test will be used for comparison between both groups, although formal power calculations for these analyses have not been performed.

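### As written, POPF by suturing method gets a separate A-versus-B Fisher test at P < 0.05 in each method, which cannot show whether the felt effect differs between methods and will often give discordant p-values when it does not

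*Protocol article*

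**What the plan says.** Three places in the protocol article bear on this.

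- **Endpoints** lists, among the secondary endpoints, "incidence of POPF by each suturing method to approximate the pancreas and the jejunum". It adds "Subgroup analyses will be planned per anastomosis or pancreatic stent" and describes these outcomes as exploratory.
- **Sample size estimation** sets the rule for secondary endpoints in general: "a hypothesis test will be used for comparison between both groups", with no formal power calculation behind it.
- **Statistical analysis plan** says that Fisher's "exact test will be used for comparison of categorical variables" and gives the threshold for P: "0.05 will be considered significant".

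Two other sections matter. Under Randomization, suturing method (mattress or non-mattress) is one of the two minimisation factors, so a two-level value exists for every patient before surgery. Under Surgical procedure, the choice of suturing technique is left free, three techniques are named as examples, and study treatment continues if the planned method changes during the operation.

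**The concern.** POPF within a suturing method is a yes/no outcome and a listed secondary endpoint. Applied literally, the rules give a Fisher test of A against B inside each method at 5%. The question a by-method endpoint raises is whether felt works differently with one method than with another. No within-method test addresses that. Each uses only part of the sample, so one can easily pass and the other fail when the true effect is identical, and a difference in significance is not a difference in effect.

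The article itself gives suturing method prominence: it is a minimisation factor, a named endpoint, and is described in the Discussion as something that may affect POPF. A table with P below 0.05 for mattress and above it for non-mattress, or the reverse, would readily be taken to mean that felt helps with one and not the other.

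**Working it through.** **Inputs from the article (Sample size estimation).** POPF is 15.5% with felt; for the control, "The incidence of POPF was 26% in a previous report without PGA felt". The error rate is "a significance level of α = 0.05 (two-sided) in a superiority design". There are 231 evaluable patients per arm and 257 per arm randomised.

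**Assumed.** The split of patients between methods is not given, so 50:50, 70:30 and 80:20 are used. The same true effect holds in every method, and the arms are balanced within method.

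**Step 1: the plan's own figure.** Two-proportion z-test, unpooled variance, 80% power:

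n = (1.96 + 0.8416)² × (0.26 × 0.74 + 0.155 × 0.845) / (0.26 − 0.155)² = 7.849 × 0.3234 / 0.011025 = 230.2, so 231 per arm. Then 231 / 0.9 = 256.7, so 257 per arm and 514 in total. Both agree with the article.

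**Step 2: power within each method.** Fisher's exact test, two-sided 5%, by full enumeration of both binomials. With p₁ and p₂ the two powers, P(exactly one significant) = p₁(1 − p₂) + p₂(1 − p₁).

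| Split | Patients per arm in each method | Power in each | Exactly one significant | Both | Neither |
|---|---|---|---|---|---|
| 50:50 | 116 / 115 | 0.449 / 0.445 | 0.494 | 0.200 | 0.306 |
| 70:30 | 162 / 69 | 0.599 / 0.267 | 0.546 | 0.160 | 0.294 |
| 80:20 | 185 / 46 | 0.663 / 0.163 | 0.610 | 0.108 | 0.282 |

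For 80:20: 0.663 × 0.837 + 0.163 × 0.337 = 0.555 + 0.055 = 0.610.

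With all 257 per arm, the discordance is 50%, 56% and 63%. If the endpoint is read as three equally frequent techniques (77 per arm each, power 0.295), some but not all are significant with probability 1 − 0.295³ − 0.705³ = 0.624.

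**Step 3: dependence on the true effect.** Control 26%, 231 per arm, counting only significant results in favour of felt:

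| Felt rate | 50:50 | 70:30 | 80:20 |
|---|---|---|---|
| 15.5% (design) | 49% | 55% | 61% |
| 18% | 39% | 41% | 43% |
| 20% | 26% | 27% | 27% |
| 22% | 15% | 15% | 15% |
| 26% (no effect) | 3% | 3% | 3% |

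**Step 4: comparison with an interaction test.** In 200,000 simulated trials per split at the design effect, a Wald test of treatment by method on the log-odds scale was significant at 5% in 4.8%, 4.5% and 4.2% of trials (50:50, 70:30, 80:20). Among trials whose overall Fisher test was significant, the two within-method verdicts were discordant in 59%, 66% and 75%.

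**Step 5: power of the interaction test in an extreme case.** Suppose felt has the design effect in one method and none in the other, at a 50:50 split with 116 per arm in each. The difference in log odds ratios is ln[(0.26/0.74) / (0.155/0.845)] = 0.650. Its variance is three terms 1/(116 × 0.26 × 0.74) plus one term 1/(116 × 0.155 × 0.845) = 3 × 0.0448 + 0.0658 = 0.200, so the standard error is 0.448. Power = Φ(0.650/0.448 − 1.96) = Φ(−0.51), about 30%.

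**The case against.** The strongest reply is that this is a condensed article. The handling of subgroups, including any interaction term, is normally left to the full protocol or analysis plan, neither of which is shown. That stands as far as it goes: a reader might infer that the trial has no interaction test, but the article neither names one nor rules one out, and its silence is no fault. What remains is what the article does fix, namely a by-method endpoint, a between-arm test for it and a threshold. An analysis plan that follows those statements carries the problem forward.

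Second, no single sentence prescribes a Fisher test inside each method. The rule comes from putting three general statements together. That is correct and makes this a reading, though by-method POPF is in the list to which the secondary-endpoint rule applies.

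Third, it might be inferred that the anastomosis and stent subgroups are tested in the same way. The article only says these analyses are planned and fixes no test for them, so the point does not extend there.

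Fourth, the outcomes are exploratory and unpowered. This lowers the weight of the point. It does not make separate tests an answer to whether the effect differs.

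Fifth, discordant subgroup p-values can arise in any trial, and an interaction test has little power here. Both are true. Low power favours estimates with intervals; it does not favour separate verdicts.

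**Conclusion.** The point holds in limited form. The stated rules lead to within-method significance tests that cannot show whether the felt effect differs by suturing method. When the effect is the same in both, they give discordant verdicts in about 49% to 61% of trials. That range requires the full design effect in each method, 231 per arm and an assumed split between 50:50 and 80:20. It is about 26-27% at a felt rate of 20%, and lower for weaker effects.

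A reader might go further and say that the trial has an even chance or better of reporting that felt works with one method and not another. The documents do not support that. The percentages are chances of discordant p-values. Nothing in the article says that a between-method conclusion will be drawn from them, and the outcomes are labelled exploratory. For the same reason, the 4-5% for the interaction test is the error rate of a formal claim, whereas the 49-61% measures how often a misreading is invited.

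The primary endpoint, sample size and primary conclusion are not affected. The change is worth making, but it is not critical.

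**What to change.** For POPF by suturing method, replace the separate within-method significance tests with one POPF model containing treatment, the mattress/non-mattress factor entered at randomisation, and their interaction. Using the value entered at randomisation keeps the grouping unaffected by changes of method during surgery. Report the A-versus-B difference with a 95% confidence interval in each method, together with the interaction p-value. State that no single method will be called significant or non-significant on its own. The same reporting can be used for the anastomosis and stent subgroups, where the article leaves the method open.

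The cost is a few sentences in the analysis plan and one extra model per modifier, with no new patients; the suturing factor is already recorded. The drawback is the low power of the interaction test (about 30% even in the extreme case worked above), so the output will mainly be estimates with confidence intervals, and a method-specific effect will seldom be claimed.
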